### Handling missing data

Missing covariate values for the subject-level information will be imputed using multiple imputation methods. All missing values will be imputed using the chained equation method that allows both categorical and continuous variables to be imputed together without making any multivariate joint distributional assumption [80]. Finally, we will combine the results from ten imputed datasets using Rubin’s formula [81].

### Aim 2: to evaluate the impact of CW on patient determinants, patient preference, and patient intention before the patient-clinician encounter

H2-1: patients in the intervention arm will show greater improvement from baseline in patient determinants (knowledge, attitude, subjective norm, perceived self-efficacy) compared to the control arm after the web intervention and before the patient-clinician encounter.

H2-2: patients in the intervention arm will be more likely to have a preference for a particular CRCS test option than those in the control arm after the web intervention and before the patient-clinician encounter.

H2-3: patients in the intervention arm will have higher intention to undergo CRCS than those in the control arm after the web intervention and before the patient-clinician encounter.

We will test Hypothesis H2*-*1 by means of linear regression analysis. We will use a separate model for each determinant. In each case, the post-web aggregated score for the scale under consideration will be used as the dependent variable. As before, the arm assignment (intervention arm versus control arm) will be the primary independent factor. The model will be further adjusted for the baseline score of the corresponding determinant and the patient-level demographic information.

Hypothesis H2*-*2 will be investigated by a logistic regression analysis with a dichotomous outcome indicating whether or not the subject has a clear preference for a CRCS test option in the patient post-web survey. This analysis will be undertaken only for the subgroup of subjects in either arm who did not have a clear preference at baseline. The demographic information will be used as independent variables as before.

Hypothesis H2*-*3 will be investigated using a model similar to that for Hypothesis H2*-*1, but the patient intention post-web will replace the patient determinants post-web as outcome, and the patient intention score at baseline will replace the patient determinants at baseline as independent variable.

### Aim 3: to evaluate the impact of CW on SDM, concordance, and patient intention during and after the patient-clinician encounter

H3-1: patients in the intervention arm will experience a higher level of SDM than those in the control arm.

H3-2: higher rates of concordance will be reached between the patient’s preferred CRCS test and the clinician’s recommended CRCS test in the intervention arm than those in the control arm.

H3-3: patient’s intention to undergo CRCS after the patient-clinician encounter will be predicted by the study arm, degree of SDM, concordance, and interaction between SDM and concordance.

We will test Hypothesis H3*-*1 by means of multiple linear regression with the OPTION score as the outcome. Otherwise the analytical strategy will be identical to that in aim 1. Hypothesis H3*-*2 will be investigated by a logistic regression analysis with a dichotomous outcome indicating whether or not the subject’s preferred CRCS test option matched with the clinician’s recommendation. Once again the analytical strategy will be similar to that in aim 1. To investigate the independent effect of SDM on concordance, we will include the OPTION score as a covariate in the regression model. Hypothesis H3*-*3 will be studied by a multiple linear regression analysis with the patient intention after the patient-clinician encounter (post-encounter) as the outcome. The primary predictors in the model will be the study arm, the OPTION score, concordance, and the interaction between the OPTION score and concordance. The interaction term allows us to investigate any differential association within SDM and intention between the concordant and the discordant groups. The model will further be controlled for the patient intention before the patient-clinician encounter. The analytical strategy will be similar to that in aim 1.

Secondary analysis will be carried out by means of Structural Equation Modeling approach to estimate the parameters of the analysis model (Figure 4) that corresponds to the conceptual model (Figure 1) [49,58-61]. Specifically, a path analysis will estimate the direct and indirect effects in order to identify the significance or otherwise of specific causal relationships. These will be done by standard *t* or *F-*tests in the context of a multiple regression analysis. Testing mediation (indirect) effects will further require using Sobel’s formula [82]. Moderation is investigated by testing for significance of hypothesized interaction terms or interaction effects that are identified during the initial screening. The analysis model will have several variables: subjective norm, perceived self efficacy, patient preference, and patient intention, each measured longitudinally; concordance, measured at one time point; practice indicators, intervention arm versus control arm, clinician communication style, SDM, and patient behavior/action each measured once along with the covariates identified during the preliminary screening. Figure 4 illustrates the full complexity of the theorized causal pathway.

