### Aim 3: to evaluate the impact of CW on SDM, concordance, and patient intention during and after the patient-clinician encounter

H3-1: patients in the intervention arm will experience a higher level of SDM than those in the control arm

H3-2: higher rates of concordance will be reached between the patient’s preferred CRCS test and the clinician’s recommended CRCS test in the intervention arm than those in the control arm.

H3-3: patient’s intention to undergo CRCS after the patient-clinician encounter will be predicted by the study arm, degree of SDM, concordance, and interaction between SDM and concordance.

Secondary analysis will employ a Structural Equation Modeling approach to understand the mechanism of the causal pathway and to test the validity of our proposed conceptual model [58-61]. Our study will provide detailed understanding of how an interactive DA that incorporates patient preference clarification and risk assessment, and that provides real-time information to the patient and the clinician during the clinic visit, will impact SDM and ultimately, CRCS adherence.

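### Aim 3 asks for the impact of ColoDATES Web on post-encounter intention, but the only regression for that outcome conditions on shared decision making and concordance, so its arm coefficient is not the total effect

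*Protocol article*

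**What the plan says.** The Aim 3 heading, in the Background and again in the Analysis section, reads: "to evaluate the impact of CW on SDM, concordance, and patient intention during and after the patient-clinician encounter". Post-encounter intention is therefore one of three things on which the impact of CW is to be evaluated.

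The hypothesis for it, H3-3, is that this intention "will be predicted by the study arm, degree of SDM, concordance, and interaction between SDM and concordance". The Analysis section specifies a multiple linear regression for it: "The primary predictors in the model will be the study arm, the OPTION score, concordance, and the interaction between the OPTION score and concordance". It then says: "The model will further be controlled for the patient intention before the patient-clinician encounter". The remaining strategy is described as similar to Aim 1.

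Two of those predictors are outcomes of the same aim. H3-1 states that "patients in the intervention arm will experience a higher level of SDM than those in the control arm". H3-2 states that "higher rates of concordance will be reached between the patient’s preferred CRCS test and the clinician’s recommended CRCS test in the intervention arm". The Background also describes the intervention process as mediated by the degree of shared decision making (SDM) and by concordance.

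Intention is measured three times (Table 2): baseline, post-web and post-encounter. H2-3 concerns the second of these: "patients in the intervention arm will have higher intention to undergo CRCS than those in the control arm after the web intervention and before the" clinic encounter.

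**The concern.** A randomised comparison supports a causal reading of the arm coefficient when the model contains only arm and variables fixed before randomisation. Once variables that arm is expected to change are added, the coefficient measures what is left after the effect passing through them is taken out. That residual has a direct-effect reading only if no unmeasured factor drives both those variables and the outcome, which randomisation does not guarantee.

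The H3-3 model is of this kind for OPTION score and concordance. If the prior-intention term is the post-web measure, it is so for a third variable as well. The Sample size and power section describes Aims 1 to 3 as comparisons between the two arms and powers continuous outcomes as a plain two-arm difference. A reader could therefore take the H3-3 arm coefficient as the answer to the Aim 3 question on intention. It could be small or null even though CW raised post-encounter intention through the route the authors propose.

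**Working it through.** **Step 1. The plan's own figure.** The Sample size and power section gives a detectable standardised difference of 0.23 for continuous outcomes, with 300 per arm and 80% power. With a two-sided 5% test, (1.960 + 0.842) × √(2/300) = 0.229, and power at 0.23 is 0.804. The figure reproduces. It describes a comparison of two arm means with nothing else in the model, so it does not describe the arm coefficient in H3-3.

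**Step 2. Each H3-3 term against the protocol's own account of it.**

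| Term in H3-3 | Relation to randomisation | Status in the protocol |
|---|---|---|
| OPTION score | after | hypothesised effect of arm (H3-1); mediator (Background) |
| Concordance | after | hypothesised effect of arm (H3-2); mediator (Background) |
| OPTION × concordance | after | product of the two above |
| Prior intention, if post-web | after | hypothesised effect of arm (H2-3) |
| Prior intention, if baseline | before | ordinary baseline covariate |

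The Randomization section places allocation after the baseline survey, which separates the last two rows. The H3-3 text does not say which applies. The Aim 2 heading uses the same before-the-encounter wording for the post-web outcome, and the Aim 2 analysis text says baseline when it means baseline. Post-web is thus the likelier reading, but it is an inference.

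**Step 3. Does another part of the plan supply the unconditioned model?**

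- H2-3 compares arms on post-web intention, before the visit, so it is a different outcome.
- The Aim 1 regression also adjusts for OPTION score, so following the Aim 1 strategy does not clearly remove it. Aim 1 does include an unadjusted test, but for screening completion, and the H3-3 terms are set out individually.
- The secondary path analysis commits to direct and indirect effects, not to a total effect.

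**Step 4. Illustrative size.** The documents give no path coefficients, so every value here is an assumption. There were 300 patients per arm and 1,000 simulated trials per row:

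- Post-web intention = 0.6 × baseline + 0.23 × arm + noise (SD 0.7)
- SDM = 0.23 × arm + 0.2 × post-web + noise (SD 1)
- Log-odds of concordance = 0.6 × arm + 0.4 × SDM
- Post-encounter intention = 0.5 × post-web + 0.25 × SDM + 0.3 × concordance + d × arm + noise (SD 0.7), where d is the direct effect

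Hand check of the total effect at d = 0:

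- through post-web intention: 0.5 × 0.23 = 0.115
- through SDM: 0.25 × (0.23 + 0.2 × 0.23) = 0.069
- through concordance: 0.3 × 0.164 (the simulated difference in concordance) = 0.049
- sum: 0.233

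Mean arm coefficient, with the share of trials with p < 0.05 in brackets:

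| Scenario | Arm + baseline intention only | H3-3, baseline intention | H3-3, post-web intention |
|---|---|---|---|
| d = 0 (full mediation) | 0.234 (90%) | 0.102 (36%) | −0.002 (5%) |
| d = 0.1 | 0.332 (>99%) | 0.200 (89%) | 0.099 (39%) |
| d = 0, plus an unmeasured cause of post-web and post-encounter intention (loading 0.4) | 0.232 (76%) | 0.088 (19%) | −0.037 (8%) |

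Coefficients are on the simulated scale. The within-arm SD of post-encounter intention was 0.92 in the first two rows and 1.11 in the third. In the third row the true direct effect is zero, yet the post-web version gives a negative coefficient.

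**The case against.** The strongest reply is that the model fits its hypothesis. H3-3 is worded as prediction by four terms, and the regression contains those four terms. Where the authors wanted an arm contrast, as in H-1 and H2-3, they wrote one. On the post-web reading H3-3 asks what the encounter adds, which is a coherent question. All of this stands, and it is why the H3-3 model should be kept. It does not settle the Aim 3 heading or the power section, both of which promise an arm comparison.

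Three stronger readings are tempting, and the documents do not support them.

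- A reader might infer that the impact on post-encounter intention is never answered. The secondary path analysis includes arm, SDM, concordance and longitudinal intention, and a total effect could be assembled from its direct and indirect effects. The accurate statement is that no specified regression gives it and the path analysis does not commit to reporting it.
- A reader might infer that the model conditions on three consequences of the intervention. Two are certain. The third rests on an unstated time point.
- A reader might infer that the arm coefficient will be null if CW works. That requires full mediation and adjustment for every path. H3-3 itself lists arm as a predictor beside SDM and concordance, which leaves room for a direct effect, and the conceptual-model figures are not available to check.

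It can also be said that a supplementary model belongs in a statistical analysis plan that is not shown. That would answer a complaint about omitted detail. Here the article fixes the model terms, and those terms do not match the stated aim.

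**Conclusion.** The point holds in limited form. The H3-3 arm coefficient is a partial effect, because the model conditions on at least two variables that the protocol hypothesises arm will change. No specified regression outside the structural equation modelling estimates the total effect of CW on post-encounter intention, which is what the Aim 3 heading asks for. The time point of the prior intention is ambiguous and changes what the coefficient means.

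How far the partial effect falls below the total cannot be known from the documents. Under the assumptions shown, without the unmeasured cause, it ranges from about 0 to 0.10 against a total of 0.23, and from about 0.10 to 0.20 against a total of 0.33. These values follow from the chosen paths and are not predictions for this trial. The screening-completion outcome of Aim 1 is outside this point. What is at risk is the interpretation of one Aim 3 result.

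**What to change.** Add, as the Aim 3 arm comparison for post-encounter intention, a linear regression on arm, baseline intention and the stratification factors (practice, gender, race). Leave out OPTION score, concordance and post-web intention. Handle clustering by clinician as in Aim 1.

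Keep the H3-3 regression as a prediction and mechanism analysis. State whether its prior intention is the baseline or the post-web measure, and state that its arm coefficient is not the total effect of the intervention.

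The cost is one more regression on data already being collected and a few sentences of analysis text. Recruitment, surveys and sample size do not change. The detectable difference of 0.23 already quoted describes a two-arm comparison of this kind, before any allowance for clustering.

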### Setting

Eleven community primary care (family medicine or internal medicine) and three university-based family medicine practices in Metro Detroit, Michigan, USA, have been recruited for the study. The community practices were recruited through a practice-based research network in the State of Michigan called the Great Lakes Research Into Practice Network. The university-based family medicine practices are operated by the department of the principal investigator. To ensure clinician and patient privacy, all practices signed a Data Sharing Agreement with the primary investigator’s academic institution. The demographics of the practices are detailed in Table 1.

**Table 1 T1:** Practice demographics

**Practice type**	**Specialty**	**Location type**	**Number of clinicians**
Community-based	Internal medicine	Suburban	2
Community-based	Family medicine	Suburban	2
Community-based	Family medicine	Urban	2
Community-based	Internal medicine	Suburban	1
Community-based	Internal medicine	Suburban	3
Community-based	Internal medicine	Suburban	1
Community-based	Family medicine	Urban	3
Community-based	Family medicine	Suburban	2
Community-based	Family medicine	Suburban	1
Community-based	Internal medicine	Urban	1
Community-based	Internal medicine	Urban	1
University-based	Family medicine	Suburban	12
University-based	Family medicine	Suburban	14
University-based	Family medicine	Suburban	4

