### Aim 1: to measure the impact of CW on patient uptake of CRCS

H-1: patients in the intervention arm will have higher rates of CRCS adherence at the six month follow-up than those in the control arm.

The study arms will be compared to assure that randomization achieved similar study population with respect to age, gender, race, previous CRCS, practice site, and data completion. Medically documented completion of CRCS will be compared between the intervention arm and the control arm by means of a chi-square test (unadjusted analysis) and a logistic regression adjusting for potential predictors at baseline. The regression analysis will be performed with data at the patient level with completing CRCS (yes/no) as the outcome measure and the arm assignment (intervention arm versus control arm) as the main covariate of interest. The practice indicator will further be included as a covariate in order to account for the variation between practices. The clustering effect due to clinician will be accounted for by using a generalized estimating equations approach. Personal patient-level background information (for example, age, race, education, marital status, smoking, health status, health insurance) from the patient baseline survey will be considered for inclusion in the regression model. The model will further be adjusted for information about the patient’s past experience with the CRCS procedures and the baseline level of patient determinants (for example, knowledge, attitude, subjective norm, self-efficacy) and intent. We will also adjust for OPTION score and pertinent clinician-level covariates such as the clinician’s communication style from the clinician survey. In order to understand whether there is any difference in the completion of CRCS rates between groups of patients who (a) complete the risk assessment tool only, (b) complete the preference clarification tool only, (c) complete both, and (d) complete neither, we will use a four level factor indicating this group membership as an independent variable in the regression model.

The contribution of a specific group of covariates will be measured by means of increase in generalized R-square defined as:$$R^{2}\left(\mathrm{increase}\right)=\exp\left(-L_{1}^{2}/n\right)-\exp\left(-L_{2}^{2}/n\right)$$where $L_{1}^{2},L_{2}^{2}$ are the likelihood ratio statistics of the smaller and larger models, respectively.

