### Sample size and power

In aims 1, 2 and 3, we make comparisons between the intervention arm and the control arm. The effect size we wish to detect between the study arms is 15%. Based on published data [48], the estimated proportion of study participants in the control arm that will complete CRCS by six months post intervention is 10 to 15%. Based on the pilot randomized controlled trial, the proportion is slightly higher (approximately 24%). We take this higher value as the anticipated rate in the control arm after six months, since this gives more conservative (larger) sample size estimates. To detect with 90% power a 15% increase in the completion rate in the intervention arm to be significant, one needs to have 213 patients per study arm. The calculation is based on a two-sided continuity-corrected chi-square test of independent proportions with 5% type-I error rate. Since we target to recruit 300 patients in each study arm, with a rough balance across practice, race, and gender, we have good power to detect such differences in the gender subgroups as well. For example, assuming that we have 150 men in each study arm, we have 76% power to detect the effect size described herein. With 300 patients per arm, a standardized mean difference of 0.23 can be detected between the two arms for continuous outcomes with 80% power. For dichotomous outcomes such as concordance, a 15% difference between the two arms can be detected with a power of ≥ 80%, when the percentage of occurrence in the control arm ranges between 25% and 50%. Thus, we are adequately powered to detect small differences for all aims. For the Structural Equation Modeling analysis, we estimate that the conceptual model will have > 100 degrees of freedom. Assuming a sample of 600 patients, power will be > 99% for a test of the overall model. Power to reject the model will be assessed by root mean square error of approximation [83].

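### The secondary path analysis specifies ordinary t or F tests although its model contains a clinician-level variable, so tests of paths from clinician communication style would exceed 5% false positives if outcomes cluster by clinician

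*Protocol article*

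**What the plan says.** The last part of the Aim 3 analysis section describes a structural equation (path) analysis that estimates direct and indirect effects. For their significance it states: "These will be done by standard *t* or *F-*tests in the context of a multiple regression analysis". For mediation it adds: "Testing mediation (indirect) effects will further require using Sobel’s formula". The variables listed for the model include "practice indicators, intervention arm versus control arm, clinician communication style, SDM, and patient behavior/action each measured once".

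The Aim 1 analysis section describes communication style as one of the "pertinent clinician-level covariates such as the clinician’s communication style from the clinician survey". The same section includes practice as a covariate and then says: "The clustering effect due to clinician will be accounted for by using a generalized estimating equations approach".

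The Aim 3 text refers back to Aim 1 for each of H3-1, H3-2 and H3-3; for H3-3 it says "the analytical strategy will be similar to that in aim 1". The paragraph on the path analysis has no such reference. It takes over only the covariates found in the preliminary screening.

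Table 1 (Setting) lists the clinicians in each practice. Sample size and power says of the path model: "Assuming a sample of 600 patients, power will be > 99% for a test of the overall model".

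**The concern.** A variable that takes one value per clinician can only be informative between clinicians. If patients of the same clinician resemble each other on the outcome, for whatever reason, an ordinary regression test counts each patient as a separate piece of evidence on that variable. Its standard error is then too small.

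Practice indicators do not cure this. They remove differences between practices, but 30 of the 49 clinicians sit in three university practices, and differences among clinicians inside a practice stay in the error term. The Aim 1 model takes the same view, since it adds a clinician-level method on top of the practice covariate.

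The stake is the interpretation of the secondary outcome. The path analysis is meant to show which links in the patient-clinician process are real. A link that starts at clinician style could be declared significant too often. Sobel's formula is built from the component coefficients and their standard errors, so any indirect effect routed through such a link carries the same error. The primary arm comparison on screening completion is not involved.

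**Working it through.** **Inputs**
- Patients: 600 (Sample size and power).
- Clinicians, from Table 1: community 2+2+2+1+3+1+3+2+1+1+1 = 19; university 12+14+4 = 30; total 49 in 14 practices.
- Test level: 5% two-sided, which the article states for the primary sample size and which is assumed here for the path tests.
- Residual clinician ICC: not given. Assumed range 0.01 to 0.20.

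**The plan's own figures.** A continuity-corrected comparison of 24% with 39% at 90% power gives 213 per arm, as stated. A noncentral chi-square test on the root mean square error of approximation (RMSEA), with 600 patients and 100 degrees of freedom and assumed pairs 0.05 vs 0.08 and 0.05 vs 0.01, gives power above 99.9%, consistent with the stated figure. The article gives no false-positive rate for the path tests.

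**Degrees of freedom for clinician style.** Five practices have one clinician, so once practice indicators are in the model they say nothing about style. The other nine hold 44 clinicians: 44 − 9 = 35, less 1 for the style coefficient = 34. The ordinary test uses nearly 600.

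**Design-effect check.** Patients per clinician m = 600/49 = 12.24. Design effect DE = 1 + (m − 1) × ICC. Actual error = 2 × [1 − Φ(1.96/√DE)].

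| ICC | DE | 600/DE | Error by formula |
|---|---|---|---|
| 0.01 | 1.11 | 539 | 6.3% |
| 0.05 | 1.56 | 384 | 11.7% |
| 0.10 | 2.12 | 282 | 17.9% |
| 0.20 | 3.25 | 185 | 27.7% |

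**Simulation.** 600 patients were placed in the Table 1 layout. The outcome was a clinician intercept plus noise. It was regressed on 14 practice indicators, arm and a null clinician-level covariate, with and without a null SDM score having the same ICC. The entries are rejection rates of the ordinary 5% t test over several runs of 2,000 to 6,000 replicates.

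| ICC | Style, equal numbers per clinician | Style, unequal numbers |
|---|---|---|
| 0.01 | 6% | 7% |
| 0.05 | 12–13% | 14–15% |
| 0.10 | 18–19% | 21–24% |
| 0.20 | 28–29% | 36% |

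At ICC 0 the style test rejects in about 5%, so the excess comes from clustering. The SDM path stays near 5% up to ICC 0.05, reaches about 6% at 0.10 and 9–10% at 0.20. The arm path stays at or below about 5% throughout.

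**After correction.** Testing style on 34 between-clinician degrees of freedom (clinician means regressed on style and practice) gives about 5% at every ICC. Clinician-robust CR2 standard errors with 34 degrees of freedom give 6–7% with equal numbers and 6–8% with unequal numbers.

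**The case against.** The strongest reply is that the path-analysis paragraph directly follows a sentence carrying the Aim 1 strategy to H3-3, under the same heading, and that the H3-1 and H3-3 models are also called multiple linear regression. A generous reader could take clinician clustering as understood, and a condensed article may leave the standard-error estimator to the analysis plan. This has some force. But the carry-over is given hypothesis by hypothesis and stops before the path analysis, which then names its own test. That is a stated choice, not only a missing detail.

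Three limits stand:
- **The paths are not visible.** The path diagram is not shown. The text lists communication style as a model variable but does not say which arrows leave it. No numbered hypothesis concerns a clinician-style effect.
- **The size is assumed.** No ICC is given. The planned model also has baseline and longitudinal patient measures that the simulation leaves out, and these could lower the residual clinician ICC. At 0.01 the excess is about one percentage point, and CR2 errors do no better there.
- **The reach is narrow.** A reader might infer that every path test is invalid. The documents do not support that: arm is randomised by patient within practice, so its paths hold their level, and SDM varies between patients of the same clinician, so its paths are only slightly affected.

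A reader might also infer that the power claim of over 99% for the overall model fails. It does not fail materially. With N cut to 384 (ICC 0.05), the same RMSEA calculation still gives over 99.9%. At 282 (ICC 0.10) it gives 99.5% and 98.2%. That deflation is itself severe, because most model variables vary within clinician.

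**Conclusion.** The point holds for paths from clinician communication style and for indirect effects that use them. The named test ignores a clustering effect that the article itself expects, and it credits such a path with nearly 600 degrees of freedom where about 34 exist. If the residual clinician ICC lies between 0.01 and 0.20, the nominal 5% test runs at about 6% to 29% with equal patient numbers per clinician, and higher with unequal numbers. Any positive ICC puts it above 5%. SDM paths run at about 5% to 9%.

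This rests on the assumed ICC range, on all 49 listed clinicians contributing patients, and on communication style being the origin of at least one tested path. Fewer contributing clinicians would mean larger clusters and a larger excess. It is a correction worth making to a secondary analysis, not a threat to the trial's main comparison.

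**What to change.** Replace the sentence on standard t or F tests with wording such as: *Path coefficients and indirect effects will be estimated with clinician as the cluster, by a two-level path model with a random clinician intercept or by clinician-robust standard errors with a small-sample correction. Paths from clinician-level variables will be tested on between-clinician degrees of freedom (about 34 with practice indicators in the model).* Sobel tests would then use these standard errors. The power statement for the overall model can stay as it is.

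The change needs no new data or patients, and it extends a principle already adopted in Aim 1. The price is wider intervals and lower apparent power for clinician-level paths, which reflects the information that 49 clinicians provide. Robust standard errors leave a small residual excess (6–8% in simulation). The two-level path model was not itself simulated; the clinician-means test on 34 degrees of freedom was, and held about 5%.
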